### Trial design

This is a prospective, controlled, randomized single-center trial evaluating the therapeutic effect of laparoscopic distal gastrectomy with D2 + CME versus conventional D2 in 336 patients with gastric cancer. Randomization is at the patient level. Participants are randomized 1:1 to receive either D2 + CME or D2.

This study is designed to evaluate the superiority of D2 + CME compared with D2 alone in terms of DFS. We are supposing differences in 3-year DFS of no less than 15% (60% in D2 vs. 75% in D2 + CME) as demonstrating superiority.

Patients enrolled in this trial are asked to complete at least 3 years of follow-up after operation. Then, with allowance, follow-up will last for 5 years. Follow-up is at 3-month intervals for the first 2 years and at 6-month intervals for the last 3 years. At every follow-up, the patients will undergo a physical examination; their nutritional status will be assessed; and blood tests (including blood count, liver function test, tumor markers) will be performed. Abdominal computed tomography (CT) and endoscopy will be performed twice annually. The date and site of the first recurrence, as well as the date of death, will be recorded. The study flow diagram is shown in Fig. 1, and the Standard Protocol Items: Recommendations for Interventional Trials (SPIRIT) checklist is provided in Additional file 1.

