### Statistical analysis

A statistical analysis plan will be developed and agreed upon by the data collection group. In summary, the continuous data will be presented as the mean ± SD and will be statistically analyzed with Student’s *t* test or the Wilcoxon rank-sum test. The categorical variables will be compared between the D2 and D2 + CME groups by the χ^2^ test or Fisher’s exact test. Grade data, including age, ASA score, and Clavien-Dindo classification, will be compared with the Wilcoxon signed-rank test. The survival curves for 3-year DFS (primary endpoints) and OS will be estimated via the Kaplan-Meier method and will be compared by log-rank test. All the *p* values are based on two-sided statistical tests; *p* < 0.05 is considered statistically significant.

Two interim analyses will be planned in this trial. The first interim analysis will be planned for the date at which half of the planned sample size has been enrolled to assess the safety of this study. The second will be held when the entire planned sample size has been enrolled. The stopping criteria in the study protocol are as follows:

1. Complication rate and mortality in the D2 + CME group are significantly higher than those in the D2 group, leading to study termination owing to the unsafety of the CME procedure

2. Survival in the D2 + CME group is significantly superior to that of the D2 group, leading to study termination owing to the efficacy of the CME procedure

3. Survival in the D2 + CME group is significantly poorer than that of the D2 group, leading to study termination owing to futility of the CME procedure

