## Trial status

This trial began recruitment in September 2014, with the first participant enrolled on 22 September 2014. Enrollment was completed on 28 June 2018.

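### The second interim look falls at full enrolment, yet its stopping criteria lead to study termination; read literally, that would end the follow-up needed for 3-year DFS while sparing almost no one the operation.

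*Protocol article*

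**What the plan says.** All references are to the protocol article.

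- **Statistical analysis, timing.** Two interim looks are planned. The first is set for the point at which "half of the planned sample size has been enrolled to assess the safety of this study". For the second, the text gives a time and no purpose: "The second will be held when the entire planned sample size has been enrolled".
- **Statistical analysis, consequence.** One list of three criteria follows, without assigning any of them to a particular look. Excess complications and mortality under D2 + CME: "leading to study termination owing to the unsafety of the CME procedure". Better survival: "leading to study termination owing to the efficacy of the CME procedure". Poorer survival: "leading to study termination owing to futility of the CME procedure". Termination is not narrowed to closing recruitment or to reporting early.
- **Trial design.** "Patients enrolled in this trial are asked to complete at least 3 years of follow-up after operation".
- **Study duration and Primary endpoint.** The 3-year follow-up of all participants is to be complete in mid-2021, and 3-year DFS is to be evaluated that year.
- **Trial status.** The first participant was enrolled on 22 September 2014. "Enrollment was completed on 28 June 2018".
- **Interim analysis.** The first look was completed on 23 September 2016, with 165 patients randomised.

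**The concern.** Stopping a trial early normally protects patients who have not yet been treated: it closes recruitment or withdraws a continuing treatment. Neither applies here at the second look. The treatment is one operation, recruitment is over by definition, and the only patients who could still be affected are the few randomised but not yet operated on. What the trial still has to do is follow patients to 3 years.

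Taken at its word, a crossed criterion would therefore end the study before most patients had contributed to the primary endpoint. The questions on 3-year DFS, overall survival and recurrence pattern would be left with immature data, and almost no trial participant would gain. The significance level does not matter here. A properly adjusted boundary at the same time, with the same consequence, would have the same effect.

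**Working it through.** **1. The plan's own figure.** The sample size compares two 3-year proportions, 0.60 and 0.75, with two-sided α of 5% and 80% power. With the pooled z-test formula and mean proportion 0.675:

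n per arm = [1.960·√(2·0.675·0.325) + 0.8416·√(0.60·0.40 + 0.75·0.25)]² / 0.15² = [1.298 + 0.550]² / 0.0225 ≈ 151.9, so 152 per arm and 304 in total.

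Adding 10% gives 152 × 1.10 = 167.2, so 168 per arm and 336 in total. Both stated figures reproduce. The calculation treats 3-year DFS status as known for the patients counted.

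**2. Accrual.** Assume uniform accrual within each reported period.

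- 22 Sep 2014 to 23 Sep 2016: 732 days (24.05 months), 165 patients, 6.86 per month.
- 23 Sep 2016 to 28 Jun 2018: 643 days (21.13 months), 336 − 165 = 171 patients, 8.09 per month.

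**3. Patients who could have 3 years of follow-up on 28 June 2018.** They must have been enrolled by 28 June 2015, which is 279 days after the start: 165 × 279/732 = 62.9, or about 63 of 336 (19%). The other 336 − 63 = 273 (81%) could not. Median potential follow-up is 168/8.09, or about 21 months.

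**4. Expected DFS events at that date.** With exponential times, the monthly hazards are −ln(0.60)/36 = 0.01419 for D2 and −ln(0.75)/36 = 0.00799 for D2 + CME. Events after 36 months are not counted, patients are split equally between arms, and losses are ignored.

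| Potential follow-up | Patients per arm | Event probability, D2 | Event probability, D2 + CME | Events, D2 | Events, D2 + CME |
|---|---|---|---|---|---|
| 36 months or more | 31.5 | 0.400 | 0.250 | 12.6 | 7.9 |
| 21.1 to 36 months | 51.0 | 0.332 | 0.204 | 16.9 | 10.4 |
| under 21.1 months | 85.5 | 0.136 | 0.080 | 11.6 | 6.8 |
| Total | 168 | | | about 41 | about 25 |

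That is about 66 events. With complete 3-year follow-up, the expected number is 168 × 0.40 + 168 × 0.25 = 67.2 + 42.0 = 109.2. The share is 66/109, or about 60%.

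**5. Sensitivity to the accrual assumption.**

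- One uniform rate over the whole actual period: about 68 patients (20%) with 3 years and about 69 events (63%).
- The 3-year enrolment period planned in the Sample size section: essentially no patient with 3 years and about 58 of 109 events (54%).

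**6. The passages side by side.** The Statistical analysis section ties termination to criteria that can be met at full enrolment. The Trial design, Study duration and Primary endpoint sections require follow-up for at least 3 years and an evaluation in 2021, with no exception for an interim stop. Nothing in the article says which prevails.

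**The case against.** The strongest reply is that termination is undefined. It could mean ending the formal comparison and reporting early while follow-up continues, and the follow-up sections, which allow no exception, are compatible with that. This stands in part. A reader might infer that a stop at the second look could do nothing except cut off follow-up, or that the rule flatly contradicts the trial's objective. The text does not go that far; the conflict arises on the literal reading. But the article does nothing to exclude that reading, and the same term serves the safety criterion, where early reporting is not its plain meaning.

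It can also be said that the list is not tied to each look, and that the full protocol or analysis plan may allocate the criteria. It is true that the article does not expressly assign all three to the second look. Yet the first look has a stated safety purpose and was reported without a survival comparison, so the survival criteria fall most naturally to the second. The point also does not rest on missing detail: the timing and the consequence are both stated, and it is their combination that causes the difficulty.

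Two further inferences are not supported.

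- **That survival should not be compared at the second look.** A look after accrual closes is legitimate. About 60% of the events is a usable amount of information under a proper boundary, and a clear early result could inform patients outside the trial; the Setting section gives about 350 laparoscopic radical gastrectomies a year at this hospital. That benefit needs early reporting, not an end to the study.
- **That the look comes too early for 30-day morbidity and 90-day mortality.** This presumes a data cut on the day of the last enrolment. The article states a trigger, not a cut-off date. Even on that presumption, at 8.09 per month only about 8 and 24 patients would be affected.

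**Conclusion.** The point holds as a conflict between stated timing and stated consequence. At full enrolment, termination would spare almost no trial patient the operation. Taken literally, it would leave about 273 of 336 patients (81%) short of 3 years, with about 66 of 109 expected 3-year DFS events observed. On the planned 3-year enrolment, essentially all patients would be short and about 54% of the events would be available.

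The share of patients with 3 years of follow-up needs only the reported dates and counts plus uniform accrual. The event counts also assume exponential DFS at the design values of 60% and 75% and no losses. The harm is conditional: a criterion must be crossed, and termination must be applied in its ordinary sense. The article reports only the first interim look, so it does not show that either has happened. If both did, the primary question would be lost for an avoidable reason, so the wording should be changed.

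**What to change.** Reconcile the Statistical analysis section with the Trial design, Study duration and Primary endpoint sections by stating that:

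1. once enrolment is complete, crossing a criterion may lead to early reporting but does not end the study;
2. all randomised patients are followed for at least 3 years after operation, whatever the second look shows;
3. the 3-year DFS analysis in 2021 is carried out in every case.

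The criteria themselves and the survival comparison at the second look can stay.

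The cost is wording in the protocol and the analysis plan. It adds no patients and no visits beyond those already planned. What is given up is the option of closing the study early on an interim crossing. Enrolment closed on 28 June 2018 and the article appeared on 9 August 2018, so the trigger for the second look had already been met at publication. Follow-up was still to run to 2021, so the clarification would still protect the primary endpoint.

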### Interim analysis

Our first interim analysis was completed on September 23, 2016. In this analysis, a total of 165 patients were recruited and randomized (D2 + CME, 82 patients; D2, 83 patients). There were no significant differences in age, sex, comorbidities, and ASA scores. The D2 + CME procedure exhibited an advantage in intralaparoscopic bleeding (23.87 ± 19.27 vs. 39.72 ± 32.28, *p* < 0.01) and lymph node harvesting (34.31 ± 11.80 vs. 25.73 ± 10.83, *p* < 0.01). The postoperative morbidity of the D2 + CME and D2 groups were 13.4% (11 of 82) and 18.1% (15 of 83), respectively (*p* = 0.412). Reoperation was required in only one case in the D2 group. The postoperative mortality was 0% in both groups. These results indicate that there is no significant difference in the complications between the D2 + CME group and the conventional D2 group. Therefore, we have ensured that this trial is safe, and thus it is ongoing.

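### Read literally, the safety stopping rule needs a significant excess in both complications and mortality, and the first interim report then takes a lack of significance as established safety

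*Protocol article*

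**What the plan says.** The Statistical analysis section of the protocol article plans two interim analyses. The first is due when "half of the planned sample size has been enrolled to assess the safety of this study", the second when the whole planned sample is enrolled. Three stopping criteria follow. The first is the safety criterion. It names two outcomes, the complication rate and mortality, joined by *and*, and is met when these in the experimental "group are significantly higher than those in the D2 group, leading to study termination owing to the unsafety of the CME procedure". The other two concern survival, significantly better or significantly poorer with D2 + CME.

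The only significance level given is two-sided 0.05, stated for all p values. No separate level is set for safety or for the interim looks. Categorical outcomes are to be compared by the chi-square "test or Fisher’s exact test".

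The Interim analysis section reports the first look: "a total of 165 patients were recruited and randomized (D2 + CME, 82 patients; D2, 83 patients"). Postoperative morbidity was 11 of 82 (13.4%) with D2 + CME and 15 of 83 (18.1%) with D2, p = 0.412. There were no deaths in either group and one reoperation, in the D2 group. The section observes that complications did not differ significantly and concludes: "Therefore, we have ensured that this trial is safe, and thus it is ongoing". The Discussion is more cautious and calls safety and feasibility only partially demonstrated.

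**The concern.** There are two linked problems.

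First, a rule that joins two outcomes by *and* can be no more sensitive than its weaker half. Here that half is mortality, which was zero in 165 patients at the first look. A clear excess of complications with little change in mortality would not meet the criterion as worded.

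Second, the interim report reasons from a non-significant test to safety. With about 82 patients per group, failing to reject says little about whether a moderate excess of complications exists. At stake is what readers may conclude about the safety of the procedure, now and when the final 30-day and 90-day results are reported by the same reasoning.

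**Working it through.** **Inputs.** From the Interim analysis section: complications 11/82 (D2 + CME) and 15/83 (D2); deaths 0/82 and 0/83. From the Sample size section: 168 per group at full enrolment. From the Statistical analysis section: two-sided 0.05, chi-square or Fisher's exact test. The true rates used for power are assumptions. The 18% complication baseline is the observed D2 rate, rounded; the mortality rates are not in the document, so a range is shown.

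**1. Reproduce the stated p value.** The pooled proportion is 26/165 = 0.1576. The difference is 0.1341 - 0.1807 = -0.0466.

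z = -0.0466 / √[0.1576 × 0.8424 × (1/82 + 1/83)] = -0.821, so chi-square = 0.674 and p = 0.412. The stated figure reproduces (Pearson, no continuity correction). Fisher gives 0.522.

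**2. Interval for the same data.** SE = √(0.1341 × 0.8659/82 + 0.1807 × 0.8193/83) = √(0.001416 + 0.001784) = 0.0566.

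The 95% CI is -0.0466 ± 1.96 × 0.0566, or -15.7 to +6.4 points (Newcombe: -15.9 to +6.6). For mortality, 0/82 has a one-sided 97.5% upper limit of 1 - 0.025^(1/82) = 4.4%.

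**3. What significance required at the first look.**
- Complications: against 15/83, at least 26/82 (31.7%, chi-square p = 0.043).
- Mortality: against 0/83, at least 4/82 by chi-square (p = 0.042) or 5/82 by Fisher (p = 0.028), about 5% to 6%.

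**4. Chance of meeting each half.** For assumed true rates, sum the binomial probabilities of all outcomes with two-sided p < 0.05 in the direction of harm.

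Mortality half (Fisher to chi-square):

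| True mortality, D2 + CME vs D2 | 82 vs 83 | 168 per group |
|---|---|---|
| 2% vs 1% | 1% to 4% | 3% to 10% |
| 3% vs 1% | 5% to 11% | 12% to 24% |
| 5% vs 1% | 22% to 31% | 46% to 59% |
| 10% vs 1% | 74% to 79% | 96% to 98% |

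Complication half at 82 vs 83 (chi-square): about 29% for 27% vs 18%, 34% for 28% vs 18%, and 75% for 36% vs 18%.

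**5. Combine.** The joint rule cannot be met more often than its smaller half. If complications doubled from 18% to 36% while mortality rose from 1% to 3%, the complication half alone would be met about 75% of the time at the first look, but the joint rule at most 5% to 11%.

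**The case against.** **The joint reading may not be intended.** The wording can be a loose way of saying either outcome. The Interim analysis section argues from complications, whereas under a strict joint rule zero deaths would have settled the matter alone. This stands as a reason to call the text ambiguous as well as restrictive, and the full protocol is not shown. A stopping rule that can be read both ways still needs its wording settled.

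**The rule is not close to impossible to trigger.** A reader might infer that it is. The document does not support this: mortality of 10% against 1% would meet the mortality half about three times in four at the first look. The low probabilities apply when mortality is low and rises modestly.

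**Excess deaths have another route.** A reader might infer that a real excess of deaths could not stop the trial. Criterion 3, poorer survival with D2 + CME, is separate and needs no excess of complications. It also requires significance, so its early power may be low, but it must be counted.

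**The safety statement rests on more than p = 0.412.** The same section reports no deaths, the only reoperation in the D2 group and a complication rate lower with D2 + CME, and the Discussion uses milder words. A reader might infer that continuing was a mistake. Nothing here shows that; the estimate favours D2 + CME and gives no sign of harm. What remains is that the stated inference runs from lack of significance to ensured safety.

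**The second look.** The article gives an express safety purpose only to the first interim, so calling the second a safety look is an inference.

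**Timing.** Enrolment closed on 28 June 2018. Rewording the criterion can no longer spare anyone the procedure. This stands, and it limits what the correction can achieve.

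**Conclusion.** The point holds in limited form. As worded, criterion 1 is not met by an excess of complications alone. Its mortality half has about a 5% to 11% chance of being met at the first look and 12% to 24% at full enrolment, if true mortality is 3% against 1%. These figures depend on assumed mortality rates and on the choice of test; the table gives the range. They also depend on the literal reading of *and*.

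Separately, and regardless of that reading, the interim data do not establish safety. They show no excess of complications, but do not exclude one of up to about 6 points, and power for 28% against 18% was about 34%. The word *ensured* goes beyond this and beyond the article's own Discussion. The fault lies in the wording of the rule and of the inference, not in the decision to continue.

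**What to change.** 1. State criterion 1 as an excess in complications or in mortality, each assessed separately with its own stated significance level. If the joint version was intended and applied, say so.
2. Replace the sentence claiming ensured safety with the estimate: complication difference -4.7 points, 95% CI -15.7 to +6.4; no excess seen, but one of up to about 6 points not excluded; no deaths in either group.
3. Report the final 30-day morbidity and mortality and the 90-day mortality as risk differences with 95% confidence intervals, and do not treat non-significance as proof of safety.

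A margin set in advance for those intervals is an option for the sponsor but is not needed to correct the text. The cost is wording and a few interval calculations, plus a less definite safety statement. With enrolment complete, item 1 mainly clarifies the record; items 2 and 3 carry the practical gain.

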### Sample size

This study was designed to evaluate the superiority of D2 + CME compared with D2 alone in terms of DFS. The sample size is calculated through two independent proportions power analysis. The calculated sample size is 304 (152 per group), with a two-sided α of 5% and an 80% statistical power (z-test) to detect a supposed 3-year DFS difference of 15% (60% in D2 group vs. 75% in D2 + CME group). Considering potential withdrawals, an additional 10% of patients will be investigated to guarantee that the final sample size is large enough. Therefore, the planned sample size is 336 (168 per group). The enrollment period will last for 3 years.

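### The rule for stopping on survival uses the ordinary p < 0.05, so one survival look at full enrolment plus the final test gives about 8% two-sided error, not 5%

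*Protocol article*

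**What the plan says.** All references are to the protocol article.

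- **Statistical analysis, tests.** DFS (primary) and OS are compared by log-rank test. All p values are two-sided, and 0.05 is the only significance level given.
- **Statistical analysis, interims.** Two are planned. The first, at half of the planned enrolment, is to assess safety. For the other: "The second will be held when the entire planned sample size has been enrolled". No purpose is given for it.
- **Statistical analysis, stopping criteria.** One list follows, not tied to either look. Criterion 1 concerns complications and mortality. Criterion 2 applies when survival with D2 + CME "is significantly superior to that of the D2 group, leading to study termination owing to the efficacy of the CME procedure". Criterion 3 applies when it is significantly poorer. Survival is not identified as DFS or OS, and no interim significance level is stated.
- **Sample size.** 304 patients (336 with the withdrawal allowance), calculated "with a two-sided α of 5% and an 80% statistical power" for a "3-year DFS difference of 15% (60% in D2 group vs. 75% in D2 + CME group"). No allowance for interim testing is mentioned.
- **Interim analysis.** The first look was completed on 23 September 2016 with 165 patients. It reports baseline factors, bleeding, lymph node yield, morbidity, reoperation and postoperative mortality, and no DFS or OS comparison.
- **Primary endpoint; Study duration.** Three-year DFS is evaluated in 2021, and three-year follow-up is complete in mid-2021.

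**The concern.** A rule that ends the trial for efficacy when a result is significant, read with a single threshold of 0.05 for all tests, gives the trial more than one chance to succeed at the full 5% level. The error rate assumed in the sample size is then not kept.

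Timing adds to the problem. At the second interim every patient has already been randomized, so an efficacy stop cannot spare anyone the inferior operation. Most patients would be well short of three years, so the claim would rest on immature data for a three-year endpoint. Estimates taken at an early efficacy stop also tend to overstate the benefit.

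**Working it through.** **1. The plan's own figure.** Two proportions, pooled variance, two-sided α 0.05, power 0.80, p₁ = 0.60, p₂ = 0.75, mean 0.675:

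n per arm = [1.960·√(2·0.675·0.325) + 0.842·√(0.60·0.40 + 0.75·0.25)]² / 0.15² = (1.298 + 0.550)² / 0.0225 ≈ 151.9, so 152.

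This gives 304, as stated. 152 × 1.10 = 167.2, rounded up to 168 per arm, gives 336. The figure reproduces with the full 5% on one test, so nothing is held back for interim looks.

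**2. Calendar.** Enrolment opened on 22 September 2014 (Trial status). There were 165 patients by 23 September 2016, about 24.0 months later (Interim analysis). Enrolment closed on 28 June 2018, about 21.2 months after that (Trial status). The final look is 36 months after the last patient.

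**3. Information fractions.** The document gives none, so these are assumptions: survival means DFS; event times are exponential with pooled three-year DFS of 67.5%, so λ = −ln(0.675)/36 = 0.0109 per month; accrual is uniform within each of the two periods.

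| | First interim | Full enrolment | Final | Fraction at full enrolment |
|---|---|---|---|---|
| Events, all follow-up | 19.8 | 68.2 | 155.2 | 68.2/155.2 = 0.44 |
| Events, follow-up capped at 36 months | 19.8 | 66.1 | 109.2 | 66.1/109.2 = 0.605 |

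**4. Overall error.** Under no difference, the statistics at information fractions t₁ < t₂ are jointly normal with correlation √(t₁/t₂). Overall error = 1 − P(|Z| ≤ 1.96 at every look).

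| Survival tested at | All follow-up | Capped at 36 months |
|---|---|---|
| Final only | 5.0% | 5.0% |
| Full enrolment + final | 8.5% | 7.9% |
| Both interims + final | 12.2% | 11.6% |

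For the middle row, varying three-year DFS from 60% to 75% moves the fraction between 0.42 and 0.61 and the error between 7.9% and 8.6%. Over a wider grid of fractions from 0.4 to 0.8 it runs from 8.6% down to 7.1%. The ratio to 5% is about 1.6 to 1.7. The chance of wrongly declaring D2 + CME superior is half the two-sided total, about 4.0% to 4.3% against 2.5%.

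**5. Maturity at full enrolment.** Only patients enrolled by 28 June 2015 have three years of follow-up. That is 279 of the 732 days to the first interim: 165 × 279/732 ≈ 63 of 336, or 19%. Half of the patients (168) fall within the last 171 enrolled, so median follow-up is about 21.2 × 168/171 = 20.8 months, or 1.7 years.

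**6. A strict boundary.** Replacing 1.96 at the full-enrolment look by 3.29 (two-sided p < 0.001) and keeping 0.05 at the end gives 5.03% at t = 0.44 and 5.01% at t = 0.605.

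**The case against.** **A separate analysis plan may set boundaries.** The article says that one will be developed and gives its methods in summary. That stands as a limit: one cannot say that the trial has no interim boundary anywhere. But the point does not rest on silence. The article states a rule (terminate if significant) and a threshold (0.05 for all p values) that together do not keep the 5% in Sample size. A boundary set elsewhere would have to override this text.

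**Survival at both interims.** Because the stopping list is not tied to a look, a reader might infer three survival tests and an error near 12%, more than double the nominal level. The article does not support that as the main reading: it gives the first look a safety purpose, and the report of that look contains no survival comparison.

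**The endpoint is not named.** This also stands. If survival means OS, the event counts and fractions differ and the percentages above do not carry over exactly. Two unadjusted tests, each able to support an efficacy claim, would remain.

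**Termination need not end follow-up.** A reader might infer that a stop at the second look cuts off the three-year data. The article does not say so. Trial design asks every patient for at least three years of follow-up, and Primary endpoint sets the evaluation in 2021. What can be said is that the efficacy claim itself would come before the endpoint is mature.

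**Criterion 3 cannot produce a false superiority claim.** Correct, which is why the one-directional figure of about 4% is given beside the two-sided total.

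**Conclusion.** The stopping rule as written does not keep the stated two-sided 5%. With one survival look at full enrolment and the final test, both at p < 0.05, the error is about 8% to 8.5%, and about 4% instead of 2.5% for a false claim that D2 + CME is superior. This assumes DFS as the survival endpoint, exponential event times, and information fractions of about 0.44 to 0.60 modelled from the trial's dates. The exact percentages depend on those assumptions, but the direction does not: any added survival test at 0.05 raises the error above 5%. About 12% would apply only if survival had also been tested at the first interim, which the article does not show. An efficacy stop at full enrolment would reduce no one's exposure to randomization and would precede a mature three-year DFS result.

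**What to change.** 1. State which interim tests survival, and whether on DFS or OS.
2. Either set a strict interim boundary, such as Haybittle-Peto p < 0.001 with the final test at 0.05 (overall error about 5.0%), or O'Brien-Fleming-type spending with the matching final level; or state that the second interim makes no efficacy test. The survival criteria need not be deleted: a stated boundary is enough, and criterion 3 is the only rule in the list that watches for worse survival with the new procedure.
3. State that follow-up to three years, and the 2021 DFS evaluation, continue whatever the interim result.
4. If the analysis plan already has such a boundary, make the protocol wording agree with it.

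The cost is a short change of wording, made before any survival comparison is run, with no extra patients. The downside is that an early efficacy claim becomes harder to make.
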